### Primary outcomes

5.1

a.The primary outcome measure is the score change in incontinence questionnaire-short form (ICI-Q-SF).Questionnaire ICI-Q-SF, scores ranging from 0 to 21, with higher scores indicating greater impairment, are compared with the baseline at the 4th (during treatment), 8th (after treatment), 24th (the first follow-up), and 32nd (the second follow-up) weeks of the study.ICI-Q-SF is the world's first universal incontinence assessment scale.^[34]^ which is mainly used to assess the frequency of incontinence, the causes of incontinence, and the impact of incontinence on the quality of life. Participants answered 4 questions related to symptoms based on their urination experience in the last week before the test. This includes the number of urine leaks, the amount of urine leakage, the impact of urine leakage on daily life, and when it occurs. The answers are recorded as 0 to 5 points, 0 to 6 points, 0 to 10 points, and the total score between 0 and 21 points. There is 1 unscored question, and the scale Cronbach's alpha coefficient was 0.92.^[34]^ The table is recommended as grade A by the Canadian urological association and the international urinary incontinence advisory committee, and as grade B by the European urological association. It is also recommended for the quantification of the severity of urinary incontinence by the UK's national institute of health and clinical excellence.b.The change in the average 24-hour urgency incontinence episodes, compared with the baseline and at the 4th, 8th, 24th and 32nd week.The 3-day urination diary is another valid, reliable and sensitive measure for patients with UUI. It has been translated into several languages, including Chinese, and is widely used in clinical records to indicate the number of urination during the day, nocturia, urgency, and urgency incontinence, as well as the amount of urine per urination and the amount of drinking water.^[35]^c.The change in the average 24-hour urge episodes, compared with the baseline and at the 4th, 8th, 24th, and 32nd week.

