### Sample size calculation

5.5

Sample size calculation for difference in response rates was done as described by Ellenberg.^[37]^ According to previous literature,^[38]^ a 40% reduction in incontinent episodes among patients receiving placebo acupuncture and a 59% reduction in incontinent episodes among patients treated with acupuncture for incontinence. We will need to recruit 50 patients per group from the Second Affiliated Hospital of Guizhou University of Traditional Chinese Medicine to obtain 80% power and a significance level of 5% while allowing for a 20% dropout rate.

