## Statistical methods and analysis

6

The data are analyzed using the SPSS software, Version 22. 0 (IBM SPSS Statistics, IBM Corp, Somers, New York). The collected data followed the intent processing principle regarding baseline characteristics, which includes all participants assigned to the group. The primary objective of the trial is to evaluate the average 24-hour urge episodes, the average 24-hour urgency incontinence episodes and the score change in the ICI-Q-SF between the groups from baseline to weeks 4,8,24, and 32. The secondary outcomes include the 3-day urination diary(the average 24-hour urine volume and the average 24-hour micturition frequency), QUID and I-QOL. Independent sample *t* test is used for comparison between the 2 groups, and in case of non-normal distribution, non-parametric Wilcoxon statistics is used to test the null hypothesis. Paired *t* test is used for comparisons before and after treatment between the 2 groups. After comparison between the groups, independent sample *t* test is used if homogeneity of variance was met, while non-parametric Wilcoxon rank sum test is used otherwise. The *χ*^2^ test is used to assess the satisfaction and safety of the treatments. A *P* < .05 indicates that a difference is statistically significant.

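### Urgency incontinence episodes are planned on percentage reductions but tested as unadjusted change in daily episodes; this costs efficiency and interpretability, not validity

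*Protocol article*

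**What the plan says.** Section 5.5 (Sample size calculation) opens with the words "Sample size calculation for difference in response rates" and takes from earlier literature "a 40% reduction in incontinent episodes among patients receiving placebo acupuncture and a 59% reduction in incontinent episodes among patients treated with acupuncture". It arrives at 50 patients per group "to obtain 80% power and a significance level of 5% while allowing for a 20% dropout rate".

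Section 5.1 (Primary outcomes) defines the second primary outcome as the "change in the average 24-hour urgency incontinence episodes, compared with the baseline", at weeks 4, 8, 24 and 32, and describes a 3-day diary as the instrument. The third primary outcome is the same kind of change for urge episodes.

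Section 6 (Statistical methods and analysis) says that an independent-sample t "test is used for comparison between the 2 groups, and in case of non-normal distribution, non-parametric Wilcoxon statistics is used". For the primary outcomes it names no baseline covariate and no percentage-change, responder or rate-ratio analysis. The document gives no baseline episode rate, SD or distribution, and section 3.1 sets no minimum or maximum episode frequency for entry.

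**The concern.** The planning figures are percentages of each group's episodes. The analysed quantity, on the natural reading of section 5.1, is an absolute change in episodes per day. These are different targets. If treatment removes a given percentage of episodes, the absolute difference depends on how many episodes patients started with, and entry criteria do not restrict that. A mean difference in daily episodes, or a rank-sum P value with no estimate, cannot be set directly against 59% versus 40%.

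The second issue is efficiency. A change score subtracts the whole baseline count. If episodes fall by 40% or 59%, follow-up tracks only 0.60 or 0.41 of baseline, so subtraction leaves baseline variation in the outcome as noise. The trial already collects the baseline diary, so the information needed to remove that noise is at hand.

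**Working it through.** **1. The plan's own figure.** Inputs from section 5.5: 0.40, 0.59, 80% power, 5% level (sidedness not stated), 20% dropout. Treated as response rates, with mean proportion 0.495:

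n per arm = [1.96 x sqrt(2 x 0.495 x 0.505) + 0.842 x sqrt(0.40 x 0.60 + 0.59 x 0.41)]^2 / 0.19^2 = 108, or 108/0.80 = 135 with dropout.

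One-sided, it is 85, or 107 with dropout. Neither gives 50. With 50 x 0.80 = 40 evaluable per arm, two-sided power for 40% versus 59% responders is 0.395. Read instead as a difference of 19 percentage points between means, 40 per arm gives 80% power only if the SD is 19 / (2.80 x sqrt(2/40)), about 30 points, which the document does not state. The sample size is a separate problem; it matters here because there is no power to spare.

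**2. Scale.** Read as percentage reductions, the planned figures leave 0.60 of baseline episodes under sham and 0.41 under electroacupuncture. The implied rate ratio is 0.41/0.60 = 0.683. The absolute difference is (0.60 - 0.41) x baseline = 0.19 x baseline:

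| Assumed mean baseline (per day) | Difference (episodes/day) |
|---|---|
| 1.5 | 0.29 |
| 3 | 0.57 |
| 5 | 0.95 |

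**3. Why subtraction is inefficient.** With a uniform response, change is -0.40 x baseline under sham and -0.59 x baseline under electroacupuncture. For an assumed baseline mean of 3 and CV of 0.6, the baseline SD is 1.8. Baseline spread alone then gives change-score SDs of 0.40 x 1.8 = 0.72 and 0.59 x 1.8 = 1.06, against a mean difference of 0.57. Diary noise and varying individual response come on top.

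**4. Power, main simulation.** 40 evaluable per arm, multipliers 0.60 and 0.41. The remaining inputs are assumed: baseline means 1.5-5 per day, between-patient CV 0.6-1.0, response CV 0.5-0.8; 12 scenarios.

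| Analysis | Power |
|---|---|
| t test on change | 14-37% |
| Additive ANCOVA on counts | 23-66% |
| Log-link model with log baseline, permutation P | 25-67% |

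The log-link model gains about 10 to 32 points over the t test at nominal size. The scale alone (log-link against ANCOVA) accounts for about -2 to +9 points, more when counts are highly dispersed.

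**5. A second simulation as cross-check.** 3-day Poisson counts, gamma baseline rates, at least one baseline episode, 800 replicates under null and alternative. Selected results at baseline 3/day, with power size-adjusted (critical value taken from the simulated null):

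| Baseline CV | SD of log response | t on change | Wilcoxon on change | ANCOVA | Negative binomial |
|---|---|---|---|---|---|
| 0.5 | 0 | 0.40 | 0.37 | 0.87 | 0.84 |
| 0.5 | 0.5 | 0.32 | 0.31 | 0.56 | 0.56 |
| 0.8 | 0.5 | 0.24 | 0.26 | 0.45 | 0.49 |
| 0.8 | 0.8 | 0.17 | 0.17 | 0.31 | 0.30 |

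Over all 12 scenarios of this set, size-adjusted negative binomial minus ANCOVA runs from -4 to +6 points. The negative binomial model reaches 80% only with no variation in individual response and a baseline of 3/day or more.

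**6. Type I error.** In the second simulation the t test and Wilcoxon ran at about 4-6%. The Wald test from the negative binomial model ran at 5-10%, so its raw power is partly inflated. This is why the permutation P value is needed.

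**The case against.** The strongest case against is that a mean difference in daily episodes is a legitimate, readable measure, that both planned tests are valid, and that the document never says treatment acts proportionally. Section 5.5 speaks of response rates, so a rate ratio of 0.68 is a construction from two group percentages and does not restore a response-rate scale either. Link functions and covariates are often left to a fuller plan. All of this limits the point. It does not remove it, because the between-group test is stated, and as stated it neither targets a reduction in percent nor adjusts for baseline.

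A reader might infer more than the documents support:

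- *That the power loss comes from not using a rate ratio.* It does not. Nearly all of the gain is baseline adjustment, and additive ANCOVA captures most of it.
- *That a rate-ratio model would secure the planned 80%.* It would not in the main scenarios.
- *That the diary counts are known to be skewed.* The document gives no distribution; it only provides a non-parametric fallback.
- *That both diary outcomes were planned on 59% versus 40%.* The percentages are given for incontinent episodes only, not for urge episodes.
- *That the trial could not report percentage reductions at all.* Group percentages follow from baseline and follow-up diary means. What is missing is a stated comparison that estimates them with an interval.

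**Conclusion.** The point holds as one of efficiency and interpretability. The planned percentage reductions and the tested change in daily episodes are on different scales, and this needs no assumption beyond the natural reading that section 5.1 means absolute change. That the difference equals 0.19 x baseline follows from the planned percentages, if they apply as proportional reductions.

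The power figures rest on assumed baseline rates and dispersion. Within those assumptions the unadjusted t test on change has roughly 14-37% power against 25-67% for a baseline-adjusted log-link model. The adjustment does most of the work, and the log scale adds about 0 to 9 points, mainly when counts are highly dispersed. There is no bias and no loss of type I error control in the planned tests. The change is worth making before unblinding.

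**What to change.** For urgency incontinence episodes, and for consistency urge episodes, replace the unadjusted t/Wilcoxon comparison of change at each stated week with one prespecified baseline-adjusted model. A suitable choice is a log-link negative binomial model of the 3-day count on arm and log(baseline count + 0.5). Take the P value from a permutation test, because the model-based test can run slightly above 5%. Report the rate ratio, also expressed as a percentage reduction, with its 95% CI beside the mean difference in daily episodes.

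If the weeks are modelled jointly, choose one of GEE or random effects in advance. Do not specify a likelihood-ratio test under GEE, which has no likelihood. The simulations above do not test a joint model across weeks.

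The change is to analysis wording only; no data collection changes. The cost is slightly more analysis work, chiefly the permutation step. It does not repair the sample size, which needs its own correction.

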**Discussion::**

This is a randomized, controlled, observer-blinded trial of electroacupuncture treatment for UUI. The results of this trial will provide more evidence on whether electroacupuncture is efficacious for treating UUI.

Advantage and Disadvantage(1)Through previous studies, electroacupuncture for UUI has been proved effective. However, there is still a lack of research on the treatment of UUI with electroacupuncture and sham electroacupuncture.(2)This trial will assess the efficacy and safety of electroacupuncture in the treatment of acute UUI and will provide high-quality, current evidence for patients and clinicians seeking safe and effective treatments.(3)In this study, we evaluated the safety of patients and clinical expectation of acupuncture, which was not common in previous studies.(4)There might be an overestimation of the electroacupuncture effect due to the small sample size of this trial.

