### The SA group

4.2

The selected non-meridional and non-acupoint points are 20 mm from the level of BL32, BL33 and BL35, and the selected acupoint are away from the second lateral line of the Bladder Meridian (Fig. 2). During the treatment, participants will lie in the prone position, the skin is disinfected as in the EA group, and the fixation pad is attached to the acupuncture point. A 1.5-inch blunt needle (from Suzhou Medical Appliance Factory of China) is used to puncture through the fixed pad into the skin surface, then evenly twisted and turned, however, without piercing the skin. Paired electrodes from the electroacupuncture apparatus were laterally connected to the needles’ handles of the bilateral sham acupoints. The dedicated power supply cord is cut off, but the appearance is as usual; that is, the electroacupuncture indicator is on, but is actually not powered on. The frequency is 5 Hz and a current intensity of 0.1 to 0.5 mA. The treatment time, waveform and SDZ-V electroacupuncture apparatus are the same as those used for the EA group. The patients are told that it an effective slight current input will be applied that may not result in a sensation of stimulation. The treatment of the 2 groups of participants will be carried out separately in different rooms to avoid communication between the participants. At the end of the trial, participants were given 10 times free compensatory treatments.

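### Safety is to be assessed only by a χ² test at P < .05, which does not give the absolute electroacupuncture risk; estimation with exact confidence intervals would serve better (minor)

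*Protocol article*

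**What the plan says.** Section 6 (Statistical methods and analysis) names the χ² test for safety in one sentence: "test is used to assess the satisfaction and safety of the treatments". The next sentence sets the threshold, a P value below .05 that "indicates that a difference is statistically significant". No risk estimate or interval is mentioned for adverse events.

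Section 5.3 lists the events. They include fainting, local hematoma, infection or abscess, severe post-needle pain, and general symptoms such as fatigue, dizziness, headache and insomnia, all recorded in both groups throughout the study. Section 5.4 adds follow-up of each event to resolution, with its severity and possible relation to treatment.

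Safety is part of the aim in the abstract, and the abstract's list of advantages says the trial "will provide high-quality, current evidence for patients and clinicians seeking safe and effective treatments".

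In section 4.1 the EA needles are inserted 50 to 60 mm. In section 4.2 the sham needle is "evenly twisted and turned, however, without piercing the skin".

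Section 5.5 fixes the size of the trial: "We will need to recruit 50 patients per group", chosen "to obtain 80% power and a significance level of 5% while allowing for a 20% dropout rate".

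**The concern.** Some of the listed harms can hardly occur in the sham arm. Hematoma, infection and abscess at the needle site require a pierced skin, and the sham needle is designed not to pierce it. For these events a comparison with sham adds little. A patient or clinician wants to know how often they happen with EA, and how high that risk could still be given the data. A χ² P value answers neither question.

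The trial was also sized for an efficacy contrast. If safety is reported through a significance test alone, a harm that matters can easily come out as non-significant, and the report would then contain no figure showing how little that result excludes. At stake is the strength of the safety statement; no efficacy conclusion is affected.

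**Working it through.** **Inputs.** 50 per arm (section 5.5). With the 20% dropout allowed there, 50 × 0.8 = 40 per arm. Forty is the low end for safety, since events are recorded throughout and patients who leave later still contribute. The threshold is P < .05 (section 6). The article gives no adverse event rate, so the rates below are assumptions: 5% and 10% with EA against 0% with sham for skin-piercing events, and 1% to 20% for the type I error check.

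**The article's own figure.** There is no safety figure to reproduce. The 50 per group comes from efficacy inputs, "a 40% reduction in incontinent episodes among patients receiving placebo acupuncture" and "a 59% reduction in incontinent episodes among patients treated with acupuncture for incontinence". Read as two proportions, with pooled value 0.495 and two-sided α = 5%:

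n = [1.96·√(2·0.495·0.505) + 0.8416·√(0.40·0.60 + 0.59·0.41)]² / 0.19² ≈ 107.5, so 108 per arm, or 108/0.8 = 135 with dropout.

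That does not return 50. It is a separate matter of efficacy sizing and plays no part here; 50 is taken as the planned size.

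**Which tables are significant.** With k affected in EA, none in sham and n per arm, the uncorrected statistic reduces to χ² = 2nk/(2n − k).

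- n = 50, k = 3: 300/97 = 3.09, P = .079.
- n = 50, k = 4: 400/96 = 4.17, P = .041.
- n = 40, k = 3: 240/77 = 3.12, P = .078.
- n = 40, k = 4: 320/76 = 4.21, P = .040.

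So χ² needs at least 4 versus 0 at either size. Fisher's two-sided P for 4 versus 0 at n = 50 is 2·C(50,4)/C(100,4) = .117. It gives .056 for 5 versus 0 and .027 for 6 versus 0, so it needs 6. At n = 40 it also needs 6 (.055 for 5 versus 0, .026 for 6 versus 0).

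**Chance of detecting the harm.** With sham risk zero this is P(X ≥ 4) for χ² and P(X ≥ 6) for Fisher, where X ~ Binomial(n, p).

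| True EA risk vs sham | n per arm | χ² detects | Fisher detects |
|---|---|---|---|
| 5% vs 0% | 50 | 24% | 4% |
| 5% vs 0% | 40 | 14% | 1% |
| 10% vs 0% | 50 | 75% | 38% |
| 10% vs 0% | 40 | 58% | 21% |

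At 5% versus 0%, χ² thus misses the harm 76% of the time with 50 per arm and 86% with 40. Fisher misses it 96% and 99% of the time.

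**False alarms.** All 2×2 tables were enumerated with the same true rate in both arms. The exact type I error of uncorrected χ² at P < .05 is:

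| True rate | n = 50 | n = 40 |
|---|---|---|
| 1% | 0.2% | 0.1% |
| 2% | 1.3% | 0.7% |
| 5% | 4.3% | 4.3% |
| 10% | 5.1% | 5.9% |
| 20% | 5.2% | 5.1% |

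The maximum over rates up to 50% is 5.7% at n = 50 and 5.9% at n = 40.

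**What estimation would show.** With zero events in n patients, the upper end of the exact two-sided 95% interval is 1 − 0.025^(1/n): 7.1% for n = 50 and 8.8% for n = 40.

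**The case against.** A reader might infer that χ² is invalid here and will raise false alarms, because 4 versus 0 is significant by χ² (.041) and not by Fisher (.117). The documents and the arithmetic do not support that. Disagreement with a conservative test is not error inflation: for rates up to 5% the exact type I error is at most 4.3%, below nominal. Nor does the article give the event rates that would make every table sparse. With equal arms, expected event counts fall below 5 only when fewer than 10 patients in total are affected. At 50 per arm the chance of that is 97% at a 5% rate, 45% at 10% and 0.2% at 20%. Some listed symptoms, such as fatigue over 24 sessions, could well be common.

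A reader might also infer that the plan equates P > .05 with safety. The article does not say so; it names a between-group test and a threshold. The low power comes from the sample size, and Fisher's test would lower it further.

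Finally, interval methods and sparse-table rules are details that a condensed article may leave to a full protocol, and naming χ² does not exclude descriptive reporting. This objection limits the point to a minor one but does not remove it. The article does fix a method for safety, and for skin-piercing events that method leaves out the most useful quantity.

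**Conclusion.** The point holds as a minor one. The single stated safety analysis is a significance test, and it does not deliver the absolute EA risk, the quantity of interest for hematoma, infection and abscess against a non-piercing sham. A non-significant result would be weak evidence on safety: under assumed risks of 5% versus 0% the test detects the harm 24% of the time with 50 per arm and 14% with 40, rising to 75% and 58% under 10% versus 0%. These figures rest on assumed rates, on a sham risk of exactly zero, and on the uncorrected χ², since the article does not say which version it means. The weakness lies in sample size and in the lack of estimation; χ² does not materially inflate the false-alarm rate of a single comparison.

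**What to change.** In section 6, make estimation the safety analysis. For each event, report the number of patients affected at least once in each arm, with an exact (Clopper–Pearson) 95% confidence interval, and the EA minus sham risk difference with its 95% interval. Base the safety statement on the upper limit for EA, and label any P value as descriptive. State that a non-significant difference is not evidence of equal safety. Do not offer Fisher's test as the remedy, given its lower power.

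The cost is a few sentences and some extra table columns, with no change to design or data collection. The safety statement becomes less favourable: even with no events observed among 50 EA patients, it would have to allow for a risk of up to 7.1%.

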## Discussion

7

The analysis of clinical trials of acupuncture treatment in UUI performed during the past 2 decades indicated that there are various methods for acupuncture treatment in UUI. Of these methods, electroacupuncture is the most frequently used, which can effectively improve symptoms such as urgency, frequent urination, and urinary incontinence. However, in clinical trials on UUI treatment with electroacupuncture, only few relevant studies included placebo control treatments,^[38,39]^ while most studies had insufficient clinical sample size^[39]^ and were performed using unclear research methods. Hence, the level of evidence obtained from these studies is not high. In this study, we are plan to compare the EA with a sham EA using standardized clinical research methods and objective quantitative evaluation indicators to verify the efficacy and safety of electroacupuncture on UUI patients. This study provides the scientific basis for a safety, more effective and easy-to-promote treatment of UUI patients in the future.

UUI patients often show urgency of urination, frequency of urination and urinary incontinence. The diagnosis is mainly based on the symptoms of the patients.^[11]^ Therefore, we use the ICI-Q-SF score, average 24-hour urge episodes and average 24-hour urgency incontinence episodes as the primary outcome to evaluate the clinical efficacy of electroacupuncture treatment of UUI. ICI-Q-SF is considered an effective, reliable and sensitive assessment method that is widely used in clinical practice.^[34]^ It is also a relatively simple questionnaire and the scores are easy to assess. Other widely used scales and questionnaires, such as the 3-day urination diary,^[35]^ I-QOL, QUID and the evaluation of clinical expectations of acupuncture, can also play subsidiary role in evaluating the results regarding the effect of acupuncture on improving the symptoms and ameliorating the quality of life of patients with UUI.

Finally, a 24-week follow-up period (9–32 weeks) is established to observe the sustained effect of electroacupuncture on UUI patients after the end of the treatment sessions. However, certain limitations are associated with this study that require to be mentioned. Owing to the characteristics of acupuncture, it is hard to blind the acupuncturists and patients. Therefore, the randomization process is tightly controlled so as to minimize the possible bias between the 2 treatments. In addition, the investigators and data analysts are also blinded. Furthermore, there might be an overestimation of the electroacupuncture effect due to the small sample size of this trial. In summary, this study can lay the foundation to design larger randomized controlled trials in the future. The results will provide more reliable evidence and elucidate the value and effectiveness of electroacupuncture in the treatment of UUI patients.

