### Study design

2.1

This is a randomized, controlled, observer-blinded trial that included 2 parallel groups with a 1:1 allocation ratio. Figure 1 shows the study flowchart.

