### Randomization and allocation concealment

2.3

The third party will be responsible for randomly grouping the participants and is strictly prohibited to participate in the treatment and data collection during the process. The random grouping is produced using the statistical product and service solutions 22. 0 (SPSS) software, and the final group assignments will be sealed in opaque envelopes. All the envelopes were numbered in the order of the sequence numbers of enrolled cases entering the clinical trial. Hence, the group assignment will be sealed inside and the sequence numbers will be printed on the outside of the opaque envelope. In addition, the acupuncturist will transfer the information of the information of random number and group assignments to each patient by phone or email.

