### Blinding

2.4

Owing to the particularity of clinical acupuncture and moxibustion, it is impossible to use a strict standard blind method for evaluation. Thus, a third party that is blind to the grouping condition carried out the effect evaluation. The efficacy evaluator, the operator and the statistician will be carried out by independent researchers. Subjects, efficacy evaluators, and statistical analysts will be all blinded.

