### The electroacupuncture group (EA)

4.1

Acupuncturists with more than 2 years of clinical experience, who have obtained the Chinese licensed physician certificate, are responsible for performing the acupuncture. The choice of intervention plan and acupoint is based on the expert's experience and based on previous studies.^[21,30–32]^ The acupoints of Ciliao (BLadder [BL]32), Zhongliao (BL33) and Huiyang (BL35) will be used (Table 1). All acupoints will be localized according to the name and location of acupoints drafted in 2006 by the National Standard of the People's Republic of China (GB/T 12346–2006). The electric stimulators (SDZ-V electroacupuncture apparatus), and stainless-steel sterilized needles (Huatuo disposable acupuncture needle; 0. 3 mm×50 mm/0. 3 mm×75 mm), were all purchased from the Suzhou Medical Appliance Factory of China. The electric stimulators will apply to the EA and to the sham electroacupuncture group (SA). During the treatment, participants will lie in the prone position, and the acupuncturists will use cotton balls soaked with 75% alcohol to sterilize the skin at the acupuncture site. After skin disinfection, sterile stainless-steel needles will be inserted into the selected acupuncture points. The needles are inserted approximately 50 to 60 mm into the skin with an angle of 60° in an inferomedial direction for BL32/BL33 and a slightly superolateral direction for BL35. After the insertion of the needle, for all needles perform small, equal manipulations of twirling, lifting, and thrusting to reach de qi (these sensations are composed of numbness, soreness, heaviness and swelling), it is considered to be an important component of acupuncture and moxibustion.^[33]^ Paired electrodes from the electroacupuncture apparatus were laterally connected to the needles’ handles of the bilateral BL32, BL33 and BL35. Acupuncture points are continuously stimulated with 100 Hz wave and a 1 to 5 mA electric current for 30 minutes. It is best to make the skin around the acupoint tremble slightly without pain. Participants were treated 3 times a week (every other day) for 8 weeks, with a total of 24 times, and 24 weeks of follow-up after treatment. The fixing pads are placed on the acupuncture points to keep the participants in a blind state.

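### Participant blinding is stated inconsistently, randomisation is credited with controlling a bias it cannot control, and no measurement named in the text tests whether the sham blind held

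*Protocol article*

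**What the plan says.** The protocol article describes the blinding of participants in several places:

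- Section 2.1 (Study design): "This is a randomized, controlled, observer-blinded trial that included 2 parallel groups with a 1:1 allocation ratio". The abstract's discussion paragraph uses the same label.
- Section 2.3 (Randomization and allocation concealment): "the acupuncturist will transfer the information of the information of random number and group assignments to each patient by phone or email".
- Section 2.4 (Blinding) opens with "Owing to the particularity of clinical acupuncture and moxibustion, it is impossible to use a strict standard blind method for evaluation", gives the effect evaluation to a blinded third party, and ends with "Subjects, efficacy evaluators, and statistical analysts will be all blinded".
- Section 4.1 (EA group): "The fixing pads are placed on the acupuncture points to keep the participants in a blind state".
- Section 4.2 (SA group) describes a blunt needle passed through a pad and "then evenly twisted and turned, however, without piercing the skin". The indicator light is on while no power is delivered, and patients hear that the current may not be felt. The two arms are treated in different rooms.
- Section 7 (Discussion), as a limitation: "Owing to the characteristics of acupuncture, it is hard to blind the acupuncturists and patients". The next sentence is "Therefore, the randomization process is tightly controlled so as to minimize the possible bias between the 2 treatments". It then adds that investigators and data analysts are blinded too.

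Section 5.1 names three primary outcomes: the ICI-Q-SF score, 24-hour urgency incontinence episodes and 24-hour urge episodes. It introduces a 3-day urination diary that records urgency and urgency incontinence. According to the abstract, expectation of acupuncture is assessed at baseline and satisfaction at weeks 4 and 8.

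**The concern.** The trial is meant to show whether electroacupuncture does more than a sham. With outcomes that patients report themselves, that comparison depends on patients not knowing their arm. A reader cannot tell from the article whether patients are blinded, intended to be blinded, or told their group. The one safeguard offered against the admitted difficulty, control of randomisation, acts on a different bias.

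If patients in either arm work out what they are receiving, part of any difference favouring electroacupuncture could be a reporting effect. Unless patients' beliefs about their allocation are recorded, the report would have no data with which to answer that challenge.

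**Working it through.** The plan states no figure on this point, so there is none to reproduce. The check is a comparison of the text, followed by one labelled illustration.

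1. **Status of the participants.** Sections 2.4 and 4.1 say or intend that subjects are blinded. Section 2.1 and the abstract claim blinding of the observer. The Discussion says patients are hard to blind, and Section 2.3, read literally, has each patient informed of the group. These statements give at least three different positions: blinded, blinding doubtful, and told the assignment.

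2. **The stated remedy.** Random allocation with concealment makes the arms comparable at entry and prevents selective enrolment. Recognition of the arm happens afterwards, over 3 × 8 = 24 sessions. However tightly the randomisation is run, it cannot limit that bias.

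3. **The blinded evaluator.** ICI-Q-SF is the patient's answers about the last week. The two episode counts are diary-type records of events, one of them a sensation, that only the patient can note. A blinded third party collects or scores these records but does not generate them, so little protection follows for any of the three primary outcomes.

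4. **What patients can feel.** In the EA arm, needles go in 50 to 60 mm, de qi is sought, and 100 Hz at 1 to 5 mA is applied until the skin trembles slightly. In the SA arm, the needle does not pierce the skin and the apparatus is said not to be powered, although the same section also lists 5 Hz and 0.1 to 0.5 mA. On either reading of the sham, the sensations differ.

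5. **What is measured.** The text names ICI-Q-SF, diary variables, I-QOL, QUID at baseline, expectation at baseline, satisfaction at weeks 4 and 8, and adverse events. Expectation precedes treatment. Satisfaction mixes belief with benefit. Neither shows whether the blind held, and no treatment-guess item is named.

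6. **Illustration of size (belief inputs assumed, not from the document).** Suppose 80% of EA and 30% of SA patients believe they receive active treatment, and that belief shifts a self-reported outcome by 0.4 SD.
   - Spurious difference = (0.80 − 0.30) × 0.4 = 0.20 SD.
   - Patients per arm: 50 recruited, or 50 × (1 − 0.20) = 40 after the planned dropout.
   - SE = √(2/n): √(2/40) = 0.224 SD; √(2/50) = 0.200 SD.
   - Shift of the test statistic: 0.20/0.224 = 0.894; 0.20/0.200 = 1.00.
   - Two-sided rejection with no true effect = Φ(shift − 1.96) + Φ(−shift − 1.96). With 40 per arm: 0.143 + 0.002 = 0.145. With 50 per arm: 0.1685 + 0.0015 = 0.170.
   - If beliefs are balanced between arms, the shift is 0 and the rate stays at 0.05.

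**The case against.** The strongest reply is that the passages can be read together. Section 2.4 itself begins by disclaiming a strict blind, so the Discussion may only be admitting that an intended blind is imperfect. Hard to blind does not mean unblinded, and a reader who infers a flat contradiction between those two statements goes further than the text. This stands. What remains is that the observer-blinded label and the transfer of assignments in Section 2.3 do not fit with blinded subjects.

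Second, the sham is built with care: pads in both arms, connected electrodes, a lit indicator, an explanation for the absence of sensation, and separate rooms. These measures address the sensory difference directly and deserve credit. They do not show that the blind succeeds.

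Third, a reader might infer that the trial never asks patients for their guess. That cannot be established: the measurement schedule in Table 2 is not shown, and the article condenses a fuller protocol. The most that can be said is that no such measurement is named in the text.

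Fourth, a reader might infer that a null result would be equally uninterpretable. In the model above, a broken blind favours electroacupuncture, so a null result despite a poor blind would count against the treatment rather than leave the question open.

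Finally, adjusting the efficacy comparison for patients' guesses conditions on a post-randomisation variable. De qi and tremor are part of electroacupuncture and would drive the guess, so adjustment could remove real effect or add bias. This objection stands and limits what the guess may be used for.

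**Conclusion.** The point holds as one of inconsistent statement, wrong reasoning and a cheap missing safeguard. The wording on participant blinding must be reconciled. The sentence crediting randomisation with control of this bias is mistaken whatever the fuller protocol says. The lack of a blinding check is established only for the measurements named in the visible text.

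The size of any bias is unknown. The illustration runs from no excess (0.05) to 0.145 or 0.170 per test, entirely according to assumed beliefs. It shows why the blind is worth measuring and is not an estimate for this trial. Nothing in the document shows that patients will in fact be unblinded, so a reader should not conclude that a positive result would be spurious. The supportable conclusion is that, without a record of beliefs by arm, a claim of efficacy beyond sham would be harder to defend. Section 2.3 may be loose wording for a sequence number or an appointment, but as printed it defeats the blind and needs correcting.

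**What to change.** - **Reconcile the statements.** Use one description of who is blinded in the abstract, Sections 2.1, 2.3 and 2.4, and the Discussion: for example, that participants are intended to be blinded and that the success of this will be examined. State in Section 2.3 that patients are not told their group.
- **Remove the claim** in the Discussion that control of randomisation limits this bias. Cite the masking measures of Sections 4.1 and 4.2 instead, and acknowledge that the primary outcomes are patient-reported.
- **Add one item** for all participants, with answers EA, sham or don't know, after an early session in week 1 and again at week 8 alongside the satisfaction form. If the full protocol already has such an item, name it in the article.
- **Report** the guesses by arm with a blinding index, and use them to qualify the efficacy conclusion. Label any outcome analysis that uses the guess as exploratory.

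The cost is one question at existing contacts, a short table and a few sentences of text. There are two small downsides: asking may prompt patients to think about their allocation, and the week-8 guess will partly reflect benefit, which is why the early guess is needed.
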